### Measures/outcomes

Because the primary objective of this trial is to evaluate feasibility and acceptability, we will assess whether the established feasibility criteria were met. To support the five quantitative criteria listed above, qualitative data will be collected from beneficiaries, their families, local stakeholders, and staff to identify qualitative themes reporting that those involved and/or effected by Group PM+ perceived it as being acceptable, feasible, and useful. Qualitative interviews will be conducted throughout the trial (see Table 3).

**Table 3 Tab3:** Qualitative interview schedule

Stakeholder	Definition	Type of interview	When
Beneficiaries/clients	Intervention (*n* = 10): participants who attended sessions regularly, those who dropped out sessions, those who improved in clinical outcomes at their follow-up assessment, those who did not improve in their clinical outcomes at follow-up, and at least one male from each of these sub-groups Control (*n* = 5): participants who improved in clinical outcomes at their follow-up assessment, those who did not improve in their clinical outcomes at follow-up, and at least one male from each of these sub-groups	Key Informant Interviews (KIIs)	After sessions of PM+ (*Rolling*)
Family	Intervention (*n* = 5): family members of participants who dropped out of sessions, family members of participants who did not (and did not) improve in their clinical outcomes at follow-up, and at least one male participant’s family from each sub-group Control (*n* = 3): family members of participants who did not (and did not) improve in their clinical outcomes at follow-up and at least one male participant’s family from each sub-group	KIIs	5 weeks after family meeting (*Rolling*)
CPSWs and helpers	Intervention (*n* = 4): CPSWs that facilitated sessions and helpers that assisted CPSWs in these sessions Control (*n* = 4): CPSWs	KIIs, Focus Group Discussions (FGDs)	After each session of PM+ training, during sessions, post-intervention
MhGap providers	Intervention and control (*n* = 2): Health workers in the local health posts that received training in mhGap	KIIs	After completion of intervention
Community Leaders	Intervention and control (*n* = 8): Community leaders (including members of mothers’ groups, local government officials, traditional healers, etc.) who received CIDT training as a part of recruitment efforts	KIIs	After completion of intervention
RAs and research staff	Intervention and control (*n* = 8): RAs and Research Supervisor	KIIs, FGDs	After completion of intervention
Psychosocial staff	Intervention and control (*n* = 3): Clinical Supervisors and counselor	KIIs, FGDs	After completion of intervention

Though the clinical outcomes in this feasibility and acceptability trial are secondary, the ability to measure them and have fewer than 15% missing items is a feasibility outcome. Clinical outcomes among participants will be measured through baseline (*t*_0_) and follow-up (*t*_1_) assessment. The baseline (*t*_0_) assessment will be conducted after the family meeting. The follow-up assessment (*t*_1_) will be scheduled 1–1.5 weeks after the fifth Group PM+ session (i.e., 8–8.5 weeks after the pre-intervention assessment). All instruments will be administered by trained research staff blind to the allocation status of the participants. The main analysis metric will be differences in primary and secondary outcomes between *t*_0_ and *t*_1_.

The primary clinical outcome measure will be the Patient Health Questionnaire (PHQ-9), a well-known 10-item instrument measuring symptoms of depression [19] (see Table 3). The measure has been clinically validated in Nepal [20]. There are eight secondary clinical outcome measures. To diminish the burden of time and questionnaires administered to the participants, many short-form versions of the assessments will be used. The WHO Disability Assessment Scale (WHODAS) has been used previously in Nepal [21–23], with excellent internal consistency between items (*α* = 0.90) and validity with multiple mental health measures for depression (*r* = 0.70, *p* < 0.001), anxiety (*r* = 0.64, *p* < 0.001), and PTSD (*r* = 0.37, *p* < 0.001). The GHQ-12 measures general psychological distress and has been clinically validated in Nepal [24]. The Psychosocial Mental Health Problems (PMHP) scale is a locally developed five-item assessment of common psychosocial problems [10]. The heart-mind screener is also locally developed and will be used to determine the acceptability of local idioms of distress and impairment due to these problems [20]. The PCL-5 (eight items) was shown in a recent study to have comparable diagnostic utility to the 20-item PCL-5 [25].

The Multidimensional Scale of Perceived Social Support (MSPSS) has been locally adapted in Nepal during a study among widows [26] and has been modified to for this trial. In the assessment, participants will assess their own connectedness with close family, friends, and other forms of support. The Reduced Tension Checklist (RTC) has been locally developed based on a coping checklist [27] to assess skill acquisition of PM+ skills. The Psychological Outcomes Profiles instrument [28] will be administered pre- and post-intervention as well as from sessions two to five for the PM+ intervention arm. The PSCYHLOPS will not be administered during session one of PM+ because of the proximity in time between pre-intervention and start of the sessions.

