### Recruitment

In the study VDCs, CPSWs will conduct awareness-raising activities to educate the public about availability of treatment for CMDs. In addition, female community health volunteers (FCHVs) and members of local community organizations (such as mothers’ groups, youth groups, etc.) will be trained on the Community Informant Detection Tool (CIDT) to identify people in the community with potential common mental disorders. The CIDT is a vignette-based tool for pro-active case detection by lay people, which has been developed and tested in Nepal [34]. The CIDT has a positive predictive value of 0.68 for adults [33]. The adapted version of CIDT for this study will include both inclusion vignettes (e.g., general distress, developed for the trial) and exclusion vignettes (e.g., psychosis, which have already been developed and validated). When community members and FCHVs identify a person in the community with symptoms of common mental disorders as described in the vignettes, they will ask them if they would like support for their stress-related problems. If people indicate they would like to receive support, then they will be told that a research assistant (RA) will visit them to conduct further screening. Individuals who meet CIDT criteria for exclusion conditions will be referred to local mhGAP-trained health workers. RAs will conduct additional recruitment by screening patients attending primary health care centers.

After screening by the RAs, CPSWs will hold a family meeting with the potential participant and a family member if they choose to have a family member participate. The family meeting will consist of (a) information about the results of the screening, (b) brief psychoeducation about the psychological consequences of adversity, and (c) information on seeking services from local health facilities with health care providers trained in basic mental health and psychosocial support. Those in the Group PM+ arm will also receive information about the intervention. Based on the family meeting, individuals can choose whether or not they want to enroll in their respective treatment arms and continue in the study.

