### Timescale

Participants for the Group PM+ trial will be recruited starting approximately 3 months after the initial CPSW training (see Table 5 for SPIRIT enrollment and assessment schedule). Group PM+ sessions will begin for those in the intervention arm within a maximum of 2 weeks after consent. Within these 2 weeks, baseline will be conducted for both arms. End line will be collected a week to a week and a half after the intervention is complete in the intervention arm and eight to eight and a half weeks after initial screening in the control arm. We anticipate that the trial will conclude by spring 2018.

**Table 5 Tab5:** Schedule of enrollment, interventions, and assessments for Group PM+

	Study period		
PARTICIPANTS (*direct beneficiaries*)—participants of Group PM+ or control arm			
	Enrollment	Baseline	Follow-up
Timepoint	*− t* _1_	*t* _0_	*t* _1_
Enrollment			
Allocation	X		
Eligibility screen	X		
Informed consent	X	X	
Interventions			
PM+	X	X	X
Control	X	X	X
Assessments			
GHQ-12	X		X
WHODAS	X		X
AUDIT	X		
Suicidality	X		
PMPH		X	X
PHQ-9		X	X
PCL-5		X	X
PSYCLOPS		X	X
RTC		X	X
TEI		X	X
Heart-mind	X	X	X
MSPSS		X	X
Tension Checklist		X	X

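### Table 3 schedules family interviews at week 5 after the family meeting, before the follow-up score that is meant to select most of those families exists

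*Protocol article*

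**What the plan says.** Table 3 (Measures/outcomes) plans 5 family interviews in the intervention arm and 3 in the control arm, each family on its own rolling clock. The time given is "5 weeks after family meeting".

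The same row says which families to choose. In the intervention arm it lists "family members of participants who dropped out of sessions". In both arms it lists "family members of participants who did not (and did not) improve in their clinical outcomes at follow-up", and asks for at least one male participant's family in each sub-group.

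The timing of the events is fixed elsewhere:
- Recruitment: "After screening by the RAs, CPSWs will hold a family meeting with the potential participant". Screening therefore precedes the meeting; the interval is not stated.
- Measures/outcomes: the baseline "assessment will be conducted after the family meeting".
- Measures/outcomes: follow-up is 1–1.5 weeks after the fifth session, which the text equates with "8–8.5 weeks after the pre-intervention assessment".
- Timescale: in the control arm, end line is "eight to eight and a half weeks after initial screening in the control arm". Baseline in both arms falls in the two weeks that follow consent.

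**The concern.** One table row gives a selection rule and a date that cannot both be followed. Whether a participant improved at follow-up is known only once t1 has been done, and the interview is due before that. Field staff would have to break either the schedule or the sampling rule, and the article does not say which gives way.

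What is at stake is the composition of a small sample. Table 2 uses families as a source on acceptability, burden, perceived benefit, contagion, retention, safety and referral, and families are well placed to say whether taking part strained relations at home. Sampling on outcome ensures that the families of people who did not improve are heard. With only 8 family interviews, losing that control could leave one side unrepresented. In addition, a PM+ family interviewed at week 5 cannot comment on the completed course.

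**Working it through.** No sample-size or error-rate formula applies; this is timeline arithmetic in weeks, with the family meeting as week 0 and the interview at week 5.

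**Inputs**
- Interview: week 5 (Table 3, Family row).
- PM+ follow-up: t1 = t0 + 8 to 8.5 (Measures/outcomes).
- g, the gap from family meeting to t0: at least 0, because baseline follows the meeting. The range 0–2 is an assumption: it takes consent as given at the family meeting and uses the two-week baseline window in Timescale.
- Control end line: screening + 8 to 8.5 (Timescale).
- s, the gap from screening to family meeting: at least 0 (Recruitment). It is not stated, so a range is shown.

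**PM+ arm:** t1 = g + (8 to 8.5); shortfall = t1 − 5.

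| g | t1 (week) | Shortfall (weeks) |
|---|---|---|
| 0 | 8–8.5 | 3–3.5 |
| 1 | 9–9.5 | 4–4.5 |
| 2 | 10–10.5 | 5–5.5 |

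The fifth session is 1–1.5 weeks before t1. Counted from t0, it falls between 8 − 1.5 = 6.5 and 8.5 − 1 = 7.5. Even with g = 0 this is after week 5, so on the article's own figures the sessions have not finished when the interview is due.

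**Control arm:** t1 = (8 to 8.5) − s; shortfall = t1 − 5.

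| s | t1 (week) | Shortfall (weeks) |
|---|---|---|
| 0 | 8–8.5 | 3–3.5 |
| 1 | 7–7.5 | 2–2.5 |
| 2 | 6–6.5 | 1–1.5 |
| 3 | 5–5.5 | 0–0.5 |
| 3.5 | 4.5–5 | none |

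Here 3–3.5 weeks is a ceiling. The conflict disappears only if the meeting comes some 3 to 3.5 weeks after screening, and the article states no such gap.

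**Sensitivity check, PM+ arm.** Suppose the stated 8–8.5 weeks is set aside and sessions are assumed weekly, with session 1 at w weeks after consent and consent at the family meeting. Then t1 = w + 4 + (1 to 1.5): week 5–5.5 for w = 0, 6–6.5 for w = 1 and 7–7.5 for w = 2. The shortfall shrinks to 0–2.5 weeks, but t1 still never comes before the interview.

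**Which parts of the rule fail.** Dropout from sessions can be seen, at least in part, by week 5. Improvement at follow-up cannot. In the PM+ arm the rule therefore fails in part. In the control arm, outcome is the only basis for selection apart from participant sex, and the sex requirement applies within the outcome sub-groups.

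**The case against.** The best defence is that this is one inconsistent cell in a supportive component, and that it is easily read too strongly. Much of that stands.

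- A reader might infer a delay of at least 3 weeks in both arms. The control schedule does not support this: it counts from screening, so 3–3.5 weeks is the most it can be.
- A reader might infer that the whole sampling rule collapses into a convenience sample. It does not in the PM+ arm, where dropouts can be partly identified.
- Read literally, the doubled negative in "family members of participants who did not (and did not) improve in their clinical outcomes at follow-up" removes improvers. It is evidently a slip: the beneficiary row lists improvers and non-improvers separately. Either reading needs t1 data.
- A reader might infer that an early family interview would bias the participant's end-line rating. Nothing in the article shows this; PM+ participants already attend five 3-hour sessions, and the PM+ family meeting already describes the intervention.
- A reader might infer that families decide progression. The qualitative criterion under Feasibility criteria names CPSWs and beneficiaries; families contribute as a supporting source.
- The beneficiary row has no matching contradiction, since an interview after the sessions can also be after t1.

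The article also does not show whether the date or the selection rule is the mistake. An interview during the intervention, with selection on attendance, would be coherent too.

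Three possible rescues fail. The rolling schedule gives each family its own clock but does not move week 5 past t1. The PSYCHLOPS ratings at sessions two to five exist only in the PM+ arm and are not the follow-up assessment that the rule names. No second family meeting is described from which the five weeks could run. Nor is this a matter of condensation for a journal, because both the date and the rule are printed.

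**Conclusion.** The point holds, with limited reach. The outcome-based part of the family sampling rule cannot be applied at the scheduled time. In the PM+ arm the interview is due about 3–5.5 weeks too early, assuming baseline 0–2 weeks after the family meeting. In the control arm it is too early by at most 3–3.5 weeks, less the unstated gap between screening and meeting, and by about 1–1.5 weeks if that gap is 2 weeks. The direction is firm for PM+ on the stated figures; for control it depends on that gap being shorter than about 3 weeks.

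The effect is confined to 8 supportive qualitative interviews. It does not touch any quantitative progression criterion. It is worth correcting because the two instructions conflict and the correction is nearly free.

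**What to change.** In the Family row of Table 3:
- Time the interviews of families sampled on clinical outcome after the participant's t1 assessment, still on a rolling basis.
- Leave interviews with families of PM+ dropouts free to take place earlier.
- Correct the definition in both arms so that it names families of participants who did, and of those who did not, improve.

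The cost is that the outcome-sampled interviews move later, by up to about 5.5 weeks in the PM+ arm and up to about 3.5 weeks in the control arm, with slightly longer recall for families. No extra interviews are needed.

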### Randomization

Two VDCs will be selected within Sindhuli district for the control and intervention arms (see Fig. 1). A meeting will be organized with the District Public Health Officer (DPHO) where VDCs will be randomly drawn for either of the trial arms. We chose to involve the DPHO in the randomization process to increase community engagement and governmental support for the research trial. The DPHO will conduct a drawing open to government staff and supervisors in the research team. CPSWs and RAs will not be present for this drawing. The DPHO will draw one of the two names out of a hat. There are several sources of potential contamination. CPSWs from both VDCs will be trained together for the initial 20-day community psychosocial training. Because of the proximity between the two VDCs, communities may be in contact with one another. CPSWs and RAs will be given a strict code of conduct to keep patient treatment confidential during the trial to reduce unblinding. Regardless, sources of potential contagions will be monitored closely and addressed in the full-scale trial after completion of the feasibility trial.

**Fig. 1 Fig1:**
[figure not shown]
Flowchart for Group PM+ cluster randomized controlled trial. Flow diagram from recruitment to end line assessment for participants/respondents in control and intervention VDCs. Gray box represents intervention. Abbreviations: CIDT, Community Informant Detection Tool (see the “Recruitment” section). VDC, Village Development Committee

### Participants

Residents of the two VDCs 18 years of age and older are eligible for enrollment. There is no maximum age for the enrollment. However, assessors will use their discretion to discontinue screening for those that are unable to properly comprehend the questions due to age or are unable to physically reach session locations within the VDC.

#### Inclusion criteria

Adults potentially with a common mental disorder are eligible to participate when they are over 18 years old and speak and understand Nepali. The General Health Questionnaire (GHQ; see below) and the WHO Disability Assessment Schedule 2.0 will be used for the screening criteria. *Screening positive* is defined as positive on all the following: score > 2 on a screening questionnaire for common mental disorders [29, 30] and score > 16 on a screening questionnaire for functional impairments [31]. Because of the lack of other services and potential benefit from participation in Group PM+, individuals with suicidality are not excluded. However, persons with current suicidal plans will be referred to the TPO counselor in addition to the invitation to participate in Group PM+.

#### Exclusion criteria

Alcohol dependency will be assessed by the alcohol use disorders identification test (AUDIT). Persons with a score of 16 and higher will be excluded from participation. WHO’s guidelines for use in primary care report that people that score below 16 can benefit from simple advice [32] and also stated that people who score 16 and higher would benefit most from simple advice plus brief counseling and continued monitoring. For this reason, potential participants who score 16 and above on the AUDIT will be excluded from the study and referred to a mhGAP-trained health professional in the area. In case of any suspected severe psychiatric disorders (e.g., psychosis) or problems (e.g., active suicidality), the individual will be referred to the health facility where health workers have been trained in mental health treatment (following mhGAP) and/or the TPO counselor in the area. For urgent treatment (e.g., active suicidality), participants will be immediately referred to the local TPO counselor and/or the nearest psychiatric services, which are available in a hospital 7 h drive from the study site. A TPO Nepal counselor and clinical supervisor for the trial will also be available to facilitate the referral process and provide follow-up psychosocial care, if and when needed. Symptoms of psychosis and severe cognitive impairment are based on clinical judgment of the assessor. The assessor (research assistant) will be given training on a community case-finding tool for detection of psychosis [33], so they can better understand clinical symptoms for exclusion (see more details below on the community case detection tool in the “Recruitment” section). If the respondent is not able to comprehend or answer the consent and/or demographic questions coherently, the questionnaire will be terminated at that point.

In addition to collecting trial outcomes, we will conduct a qualitative component. We will conduct key informant interviews (KII) and focus group discussion (FGD) and collect process notes. For the qualitative component, we will select a subsample of intervention and control arm participants for KIIs and focus group discussions. In addition, we will conduct KIIs with CPSWs, family members of the participants, research staff, community officials, and primary health care staff.

### Recruitment

In the study VDCs, CPSWs will conduct awareness-raising activities to educate the public about availability of treatment for CMDs. In addition, female community health volunteers (FCHVs) and members of local community organizations (such as mothers’ groups, youth groups, etc.) will be trained on the Community Informant Detection Tool (CIDT) to identify people in the community with potential common mental disorders. The CIDT is a vignette-based tool for pro-active case detection by lay people, which has been developed and tested in Nepal [34]. The CIDT has a positive predictive value of 0.68 for adults [33]. The adapted version of CIDT for this study will include both inclusion vignettes (e.g., general distress, developed for the trial) and exclusion vignettes (e.g., psychosis, which have already been developed and validated). When community members and FCHVs identify a person in the community with symptoms of common mental disorders as described in the vignettes, they will ask them if they would like support for their stress-related problems. If people indicate they would like to receive support, then they will be told that a research assistant (RA) will visit them to conduct further screening. Individuals who meet CIDT criteria for exclusion conditions will be referred to local mhGAP-trained health workers. RAs will conduct additional recruitment by screening patients attending primary health care centers.

After screening by the RAs, CPSWs will hold a family meeting with the potential participant and a family member if they choose to have a family member participate. The family meeting will consist of (a) information about the results of the screening, (b) brief psychoeducation about the psychological consequences of adversity, and (c) information on seeking services from local health facilities with health care providers trained in basic mental health and psychosocial support. Those in the Group PM+ arm will also receive information about the intervention. Based on the family meeting, individuals can choose whether or not they want to enroll in their respective treatment arms and continue in the study.

### Blinding and concealment

CPSWs, RAs, trial participants, and local mhGAP-trained health workers will be blinded to the conditions of the two arms. Facilitators in the intervention arm and CPSWs in EUC will be instructed not to disclose the treatment that any participants are receiving except with their clinical supervisors. Assessors will be asked at baseline to indicate what treatment they think each participant will receive. Assessors will be asked the same question at end line for each participant. This will provide some data on the amount of unblinding that might occur in the RCT. Study statisticians will be blinded to treatment arm during analysis.

